#### Safety

The protocol will be performed with a commercialized ultrasound scanner. This is considered a noninvasive and very safe examination [24]. The technology is widely used to assess the elastic properties of peripheral muscles without any adverse outcomes [15, 25]. Previous studies have reported the use of SWE during pregnancy for both mother and fetal tissue assessment without any adverse outcomes. Therefore, the use of SWE for the assessment of the pelvic floor muscles of pregnant women is safe [26, 27].

### Data collection

#### Women’s characteristics

At the first visit, after validation of the inclusion and exclusion criteria, we will collect anthropometric data about the women: height (in cm), weight (in kg) and BMI (in kg.m^− 2^). Demographic data and obstetric history will also be collected during the first visit: age (in years), gestity, and verification of the absence of a previous delivery (cesarean or vaginal). The dominant side will be recorded: right-handed or left-handed.

#### Clinical pelvic floor assessment

We will perform a clinical pelvic floor assessment at each visit. This examination will follow the recommendation of the Pelvic Organ Prolapse Quantification system (POP-Q) [28]. We will perform the procedure with women in the lithotomy position after voiding and maximal strain on the Valsalva maneuver. The position of each point of the POP-Q will be expressed in negative or positive values (in cm), and the length of each segment of the POP-Q (genital hiatus (gh), perineal body (pb), total vaginal length (tvl)) will also be expressed in centimeters [28].

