## Methods

### Design

The ELASTOPELV study will be a prospective, longitudinal, monocentric study. The scheme of the study will involve 3 visits during pregnancy: the first one between 14 and 18 weeks, the second between 24 and 28 weeks and the last between 34 and 38 weeks of pregnancy (Fig. 1). For each of these three visits, the protocol will follow these steps: clinical perineal assessment, ultrasound B-mode perineal assessment, SWE assessment of the *levator ani* muscle, the external anal sphincter, the *biceps brachii* muscle and the *gastrocnemius medialis* muscle (Fig. 1).

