#### Ultrasound B-mode pelvic floor assessment

We will perform an ultrasound B-mode pelvic floor assessment at each visit of the study. This examination is performed with the woman in the lithotomy position after voiding. We will use an Aixplorer® device with an XC6–1 1–6 MHz abdominal curved probe (V12, Supersonic Imagine, France). We will measure the anteroposterior hiatal diameter (distance between the antero-inferior extremity of the pubic symphysis and the anorectal junction, in cm) at rest, during a maximal strain on the Valsalva maneuver and at maximal perineal contraction. For these measures, we will use the translabial perineal ultrasound approach widely described by Dietz et al. [29, 30]. We will ask women to perform two initial Valsalva maneuvers with biofeedback instruction to prevent levator coactivation from serving as a confounding factor in our analysis [31].

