For this assessment, we will use the procedure that we described for nonpregnant women in a previous publication [13]. The examination will be performed with the woman in the lithotomy position after voiding. We will first locate the *levator ani* muscle at its pubic insertion during a B-mode ultrasound using the procedure described by Dietz et al. for the diagnosis of levator avulsion, with 87% agreement between observers. We will place the probe in the sagittal plane on the perineum and apply a 10° parasagittal inclination to identify the muscle (Fig. 2) [32]. We will perform assessments during the three considered conditions: rest, stretch and subjective maximal contraction. For the stretch condition, the woman will be asked to perform a maximal Valsalva maneuver. We will prevent levator coactivation in the same way that we described for ultrasound pelvic floor assessment [31]. With this procedure, a previous study reported that the shear modulus measured in *levator ani* muscle in non pregnant women is about 16 kPa at rest and 35 kPa during Valsalva maneuver [13].
Specificity for external anal sphincter assessment

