#### Concordance between SWE measurements and clinical / ultrasound measurements

We expect to report an association between the elastic properties of the *levator ani* muscle and the clinical and ultrasound assessments of pelvic floor distension. For the clinical assessment, we will investigate all POP-Q measurements but with a special interest in the gh and pb measurements that are performed during the Valsalva maneuver and that reflect pelvic floor distension that occurs during the maneuver. A similar association will be investigated for the ultrasound assessment (distance between the pubic symphysis and the anorectal angle). If we can report such a correlation between the elastic properties of the *levator ani* investigated using SWE and clinical / ultrasound pelvic floor distension, it will support the efficiency and the applicability of SWE for functional pelvic floor muscle assessments. We choose to focus on the *levator ani* muscle for this analysis given the well-reported association between levator hiatus and pelvic organ mobility [46].

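### POP-Q is taken at maximal Valsalva before each visit's biofeedback, whereas the B-mode and levator SWE measures it is compared with are taken after it

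*Protocol article*

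**What the plan says.** **Order.** *Design* sets the sequence for all three visits: "For each of these three visits, the protocol will follow these steps: clinical perineal assessment, ultrasound B-mode perineal assessment", followed by SWE.

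**POP-Q.** *Clinical pelvic floor assessment* reads: "We will perform the procedure with women in the lithotomy position after voiding and maximal strain on the Valsalva maneuver". It adds no coaching or biofeedback step and no cross-reference to one.

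**B-mode.** *Ultrasound B-mode pelvic floor assessment* has women "perform two initial Valsalva maneuvers with biofeedback instruction to prevent levator coactivation from serving as a confounding factor in our analysis".

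**Levator SWE.** The levator part of *Shear wave elastography assessments* carries this over: "We will prevent levator coactivation in the same way that we described for ultrasound pelvic floor assessment".

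**Use of the measures.** *Judgment criteria* makes the association of POP-Q with levator modulus at each visit a secondary criterion and singles out gh and pb. *Plan of analysis* uses Spearman coefficients at each trimester for the associations and a Friedman test for change over visits. *Concordance between SWE measurements and clinical / ultrasound measurements* refers to "gh and pb measurements that are performed during the Valsalva maneuver and that reflect pelvic floor distension that occurs during the maneuver", and says that a correlation with modulus would support the applicability of SWE.

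**The concern.** The protocol names a confounder of the Valsalva, controls it for two measures and, as written, leaves it uncontrolled for a third that is then correlated with one of those two. Two results could suffer.

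- **Correlation.** A woman who contracts her levator while straining shows a smaller gh at POP-Q than her tissue would allow. Her modulus during Valsalva is read later in the visit, after biofeedback. The POP-Q correlation therefore mixes two conditions, while the B-mode correlation uses one. If the two correlations differ, preparation is a possible explanation alongside the measure itself.
- **Change over visits.** At visit 1 the POP-Q comes before any study biofeedback. At visits 2 and 3 women have already been instructed once or twice. If they retain that instruction, gh would rise without any change in tissue. This is the same direction as the hiatal enlargement in pregnancy that *Power calculation* cites, so it could pass for a real finding.

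**Working it through.** The plan states no figure on this point, so there is none to reproduce. The check sets the sections side by side and then illustrates size under assumptions.

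**1. Valsalva control by measure, as written**

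| Measure | Place in visit | Coactivation control |
|---|---|---|
| POP-Q (gh, pb) | first | none stated |
| B-mode hiatal diameter | second | two biofeedback Valsalvas |
| Levator SWE | after B-mode | same as B-mode, by cross-reference |

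Following the stated order, POP-Q always precedes that visit's biofeedback.

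**2. Change over visits**

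From the document: three visits, Friedman test, significance at 0.05, at least 50 women analysed. Assumed: no true change in gh, within-woman correlation 0.7, coactivating women read *d* = 0.5 or 1 SD low, prevalence of coactivation at visits 1/2/3 as shown. There were 3,000 simulated studies per row; the Monte Carlo standard error at 5% is √(0.05 × 0.95 / 3000) = 0.4 percentage points.

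The expected false shift from visit 1 to visit 3 is *d* × (p1 − p3). For 40/30/20% it is 0.5 × 0.20 = 0.10 SD or 1 × 0.20 = 0.20 SD.

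| Prevalence at visits 1/2/3 | False shift, SD (*d* = 0.5 / 1) | Friedman rejection (*d* = 0.5 / 1) |
|---|---|---|
| 0/0/0% | 0 / 0 | 5% / 5% |
| 40/40/40% | 0 / 0 | 5% / 5% |
| 40/30/20% | 0.10 / 0.20 | 9% / 18% |
| 40/20/10% | 0.15 / 0.30 | 14% / 34% |
| 40/10/0% | 0.20 / 0.40 | 25% / 61% |

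A variant with 48 women (60 × 0.8), within-woman correlation 0.6 and readings lowered at visit 1 only (complete retention) gave 10% to 18% rejection with 20% coactivators and 24% to 62% with 40%. The driver is the fall in coactivation, not its level.

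**3. Correlation at one visit**

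Assumed: n = 50, true correlation of gh with modulus −0.4, 40% coactivate at POP-Q. Let λ be the correlation between modulus and the latent tendency to coactivate.

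*Coactivation unrelated to modulus (λ = 0).* The variance of observed gh becomes 1 + d² × 0.4 × 0.6, so the Pearson correlation is
- d = 0.5: −0.4 / √1.06 = −0.389
- d = 1: −0.4 / √1.24 = −0.359

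*Coactivation related to modulus, d = 1.* The covariance is −0.4 − 0.386λ, where 0.386 is the normal density at the 60th percentile. The variance is 1.24 + 2 × 0.4 × 0.386λ.
- λ = 0.3: −0.516 / √1.333 = −0.447
- λ = 0.5: −0.593 / √1.394 = −0.502
- λ = −0.5: −0.207 / √1.086 = −0.199

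The simulated mean Spearman coefficients, which run slightly closer to zero than Pearson, agree:

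| Scenario | Mean Spearman | Share with p < 0.05 |
|---|---|---|
| No coactivation | −0.38 | 79% |
| d = 0.5, λ = 0 | −0.37 | 76% |
| d = 1, λ = 0 | −0.34 | 69% |
| d = 1, λ = 0.3 | −0.42 | 88% |
| d = 1, λ = 0.5 | −0.48 | 95% |
| d = 1, λ = −0.5 | −0.18 | 24% |

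The correlation can move either way. Only gh was modelled; the size and sign of any effect on pb are not known from the document.

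**The case against.** **Silence is not proof.** The POP-Q section does not say that biofeedback is withheld. It follows a cited POP-Q recommendation, and a condensed article may leave coaching of the strain to the full protocol. This stands as a caution on wording. But the article does describe the control: it places it at the ultrasound step, extends it by name to levator SWE, and states an order that puts POP-Q before it. The asymmetry lies in what the text fixes.

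**A reader might infer that the POP-Q trend is biased.** The document does not support that. A false trend needs coactivation to change between visits. Consecutive visits are at least 6 weeks apart (24 − 18 and 34 − 28), the instruction is part of an assessment done at every visit, and nothing is said about retention. The large rejection rates above come from assuming a steep fall. This objection stands, so the trend concern is conditional.

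**A reader might also infer that the correlation is weakened.** That too is unsupported as a general statement. If coactivation is unrelated to modulus, the loss is at most about 0.04, small against a sampling error of roughly 1/√(50 − 3) = 0.15 on the Fisher scale. If it is related, the correlation may strengthen.

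**Scope is limited.** The primary criterion does not use POP-Q, the B-mode correlation has one rule throughout, and no formal test between the POP-Q and B-mode correlations is planned. All of this is correct. What remains is a secondary association whose interpretation is harder than it needs to be.

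**Conclusion.** The point holds as an avoidable inconsistency in secondary measures. Under the stated order, POP-Q is read before the control that the protocol considers necessary for the measures it is compared with. The POP-Q versus levator modulus correlations may therefore be distorted in an unknown direction. The change in POP-Q over visits may be biased if coactivation declines after the first instruction, and is not biased by this route if coactivation stays constant.

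The mismatch of control itself needs no assumption about carry-over between visits; for it to matter, some women must coactivate, which is the protocol's own reason for the biofeedback step. Every figure for size rests on assumed prevalence, effect, within-woman correlation, true correlation and link to modulus, and shows a range, not an estimate.

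The primary shear-modulus endpoint is unaffected: it does not use POP-Q, and by the stated order the SWE readings follow that visit's biofeedback. This is a cheap improvement, not a threat to the study's main result.

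**What to change.** - **Order.** In *Design*, give the two existing biofeedback Valsalvas at the start of each visit, or do the B-mode step before POP-Q.
- **Rule.** In *Clinical pelvic floor assessment*, state that POP-Q is read under the same coactivation control as B-mode and levator SWE. If this is already done in practice, that sentence together with the corrected order settles the matter.
- **Women already enrolled.** Keep one order within each woman, or record the order used at each visit. Interpret with caution any gh or pb change that spans a switch of order or the first instruction. The caution cannot be confined to visits 1 to 2, because a switch between visits 2 and 3 would affect that interval as well.

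**Cost.** Existing steps are rearranged within the visit, with no new procedure or equipment. The downside is that women measured in the old order are not fully comparable on POP-Q with those measured in the new one, and changing order partway through a woman's follow-up could itself create an uncontrolled-to-controlled step. Hence the rule for enrolled women.

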#### Ultrasound B-mode pelvic floor assessment

We will perform an ultrasound B-mode pelvic floor assessment at each visit of the study. This examination is performed with the woman in the lithotomy position after voiding. We will use an Aixplorer® device with an XC6–1 1–6 MHz abdominal curved probe (V12, Supersonic Imagine, France). We will measure the anteroposterior hiatal diameter (distance between the antero-inferior extremity of the pubic symphysis and the anorectal junction, in cm) at rest, during a maximal strain on the Valsalva maneuver and at maximal perineal contraction. For these measures, we will use the translabial perineal ultrasound approach widely described by Dietz et al. [29, 30]. We will ask women to perform two initial Valsalva maneuvers with biofeedback instruction to prevent levator coactivation from serving as a confounding factor in our analysis [31].

#### Shear wave elastography assessments

As previously stated, an assessment of the elastic properties of the pelvic floor muscles of pregnant women will be performed at each visit using SWE. These measures will be performed for the *levator ani,* the external anal sphincter, *biceps brachii and gastrocnemius medialis* muscles. Each measurement will be performed on the right side of the woman, as it would be ideal to obtain all the measurements for the same side, preferentially while the women are in left lateral decubitus, which offers the possibility of accessing the right limbs. For each muscle’s location, we will investigate the muscle during three conditions: rest, stretch and subjective maximal contraction. We will use an Aixplorer® device (V12, Supersonic Imagine, France) with a linear SL 18–5 probe (5–18 MHz). Every measure will begin by performing a B-mode procedure to locate the muscle. Then, we will proceed with recording a 10-s video clip of the SWE measurements. The region of interest will be outlined by hand and the measure of the shear modulus will be obtained within this region in postprocessing. For assessment at rest and during a stretch, we will consider the mean shear modulus of the video clip, whereas for assessment during contraction, we will consider the maximal shear modulus.

We will perform three measures for each condition (rest, stretch and contraction) and consider the mean of the three measures for analysis. We choose to consider the mean of the 3 acquisitions for each condition to maximize the reliability of the measurement by considering all the measures (the most intense and the weakest contraction, the first measure after installation, etc.)

As previously mentioned, we will measure the Young modulus using the Aixplorer® device, which will be divided by a factor of 3 to obtain the shear modulus, which is more accurate for anisotropic tissues such as muscle [23].

One single investigator will perform all the measurements.
Specificity for the *levator ani* muscle assessment

For this assessment, we will use the procedure that we described for nonpregnant women in a previous publication [13]. The examination will be performed with the woman in the lithotomy position after voiding. We will first locate the *levator ani* muscle at its pubic insertion during a B-mode ultrasound using the procedure described by Dietz et al. for the diagnosis of levator avulsion, with 87% agreement between observers. We will place the probe in the sagittal plane on the perineum and apply a 10° parasagittal inclination to identify the muscle (Fig. 2) [32]. We will perform assessments during the three considered conditions: rest, stretch and subjective maximal contraction. For the stretch condition, the woman will be asked to perform a maximal Valsalva maneuver. We will prevent levator coactivation in the same way that we described for ultrasound pelvic floor assessment [31]. With this procedure, a previous study reported that the shear modulus measured in *levator ani* muscle in non pregnant women is about 16 kPa at rest and 35 kPa during Valsalva maneuver [13].
Specificity for external anal sphincter assessment

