The choice of the transperineal approach to assess pelvic floor muscles is supported by an important literature reporting that such an approach is efficient (in terms of acceptability and reliability) to investigate pelvic floor muscles [29, 30, 32, 33]. In 2018, our research team published a feasibility study on the use of SWE to investigate the elastic properties of the *levator ani muscle* in nonpregnant women with this transperineal approach [13]. In this paper, we report that we were able to individualize the *levator ani* muscle and to measure a shear modulus in 100% of women with a lower than 35Kg.m^− 2^ BMI which allows to report the feasibility of the procedure. We consider that the fact that we investigate only the right *levator ani* muscle do not induce any bias considering that in this previous study, we reported that there are no differences between the elastic properties of the right and left *levator ani* muscles, assessed using SWE [13]. There is no published technique for investigating in vivo the elastic properties of the external anal sphincter. Considering the easy access to the external anal sphincter using ultrasound with a transperineal approach and the efficiency of SWE in other muscle applications, we consider that this choice is relevant [33]. In the future, this examination could be easily performed in the ultrasound follow-up of pregnant women. We do not have data about the reproducibility of pelvic floor muscles assessment using SWE. Nevertheless, considering the easy access to these muscles with a transperineal approach and the fact that SWE is a reliable tool for assessing peripheral muscles we expected a good reproducibility of the technique.

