### Expected results

#### Concordance with animal experimentations

As we mentioned in the background section, human data about the evolution of pelvic floor muscles during pregnancy are lacking. It has been reported in animal experiments that during pregnancy, the stiffness of the pelvic floor muscle increases due to a drastic increase in total collagen content [9–11]. As we mentioned it in the background section, these animal experimentation related data must be interpreted carefully considering that there is no work with a confirmation that these phenomena occur in a same way in pregnant women.

We expect to report a similar increase in the stiffness of the pelvic floor muscles during pregnancy in our study, which will support the data from animal experiments. Such an increase in stiffness might be a protective process from perineal trauma given that tissue with the lowest stiffness easily raises their plasticity threshold to a level beyond which irreversible damage occurs in the tissue [12].

One potential confounding factor for the interpretation is that we do not have data about the use of perineal stretching device such as Epi-No® during pregnancy. There is no data about the impact of such a practice on pelvic floor muscle elastic properties. Some works reports an increase in perineal extensibility, but it reports maximal vaginal compliance to the Epi-No® without data about a direct assessment of pelvic floor muscles stiffness [44, 45]. Furthermore, its use is not recommended in French guidelines [36]. This considered, we think that the risk of bias in our cohort is weak.

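### The primary shear modulus is read from hand-outlined regions with no masking to visit described, and the triplicates are averaged without a repeatability estimate

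*Protocol article*

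**What the plan says.** All references are to the protocol article.

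- **Outcome.** Under Judgment criteria, the primary criterion is the evolution of the shear modulus of the levator ani and external anal sphincter across pregnancy, at rest, during Valsalva and during contraction.
- **Reading.** Under Shear wave elastography assessments, a 10-second clip is recorded and then: "The region of interest will be outlined by hand and the measure of the shear modulus will be obtained within this region in postprocessing". Rest and stretch use the mean over the clip, "whereas for assessment during contraction, we will consider the maximal shear modulus".
- **Operator.** The same section states: "One single investigator will perform all the measurements".
- **Replicates.** "We will perform three measures for each condition (rest, stretch and contraction) and consider the mean of the three measures for analysis". The reason given is "to maximize the reliability of the measurement by considering all the measures". The Plan of analysis lists Friedman tests, Spearman correlations and logistic regression, and gives the replicates no other use.
- **Expectation.** Under Concordance with animal experimentations: "We expect to report a similar increase in the stiffness of the pelvic floor muscles during pregnancy". The section on the choice of peripheral muscles expects the biceps to follow a different pattern.
- **Reproducibility.** Under the choice of shear wave elastography: "We do not have data about the reproducibility of pelvic floor muscles assessment using SWE". Good reproducibility is expected from easy access and from results in peripheral muscles. The same section says that no in vivo technique has been published for the sphincter.

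**The concern.** Each woman is her own comparator, and visit coincides with gestational age. If regions are outlined slightly differently at late visits than at early ones, the result has the same form as the hypothesised rise. Outlining by hand involves judgement, and the article states which direction the team expects. Because the region is drawn after the scan, this step could be masked at little cost, but the article does not describe masking.

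The second part is the missing error estimate. The authors raise reproducibility themselves and answer it with an expectation, although three acquisitions per condition would already allow one component of error to be estimated. At stake are the credibility of the primary result and its use for planning: the Discussion hopes the data will support a power calculation for a larger study, where measurement error matters.

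**Working it through.** The article gives no SD, ICC or reading error for its own measurements, so there is no stated figure to reproduce. The drift sizes and ICCs below are assumptions. They show sensitivity and do not estimate what will happen.

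**1. What the text establishes**

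| Element | In the article? |
|---|---|
| Region outlined by hand, in postprocessing | Stated |
| One investigator for all measurements | Stated |
| That investigator also outlines the regions | Natural reading of the two statements together; not stated outright |
| Expected direction of change | Stated (increase) |
| Masking of clips to visit | Not mentioned either way |
| Reproducibility data for pelvic floor SWE | Stated as absent |
| Use of triplicates | Averaged; no other use given |

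**2. Directional drift and the planned test**

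Inputs: Friedman test over 3 visits and alpha 0.05 (Plan of analysis); 50 women (Power calculation). Assumptions: no true change, independent normal residuals with SD 1 at each visit, and reading shifts of 0, b/2 and b at visits 1, 2 and 3.

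Statistic: Q = 12/(n·3·4) × Σ R_j² − 3·n·4, where R_j is the rank sum of visit j, compared with the 95th percentile of chi-square on 2 df. Simulation with 10,000 runs:

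| Total drift b (residual SD) | Rejection rate, n = 50 |
|---|---|
| 0 | 5.0% |
| 0.2 | 10.7% |
| 0.3 | 17.7% |
| 0.5 | 44.3% |
| 0.8 | 85.7% |

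With 48 women (60 inclusions × 0.8) the rates for b = 0.3 and 0.5 are 18.2% and 44.3%.

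**3. The same question for a paired comparison**

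With 48 women the 95% half-width for a paired change is t(0.975, 47)/√48 = 0.290 SD of the change. A shift of exactly that size makes a paired t-test significant in about half of studies, by construction, since the expected statistic then sits at the critical value. With independent residuals this equals 0.290 × √2 = 0.41 residual SD. Under the planned Friedman test the same shift gives about 32% if it is linear over visits and about 40% if it affects only the last visit.

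**4. What averaging does**

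Reliability of a mean of three is 3r/(1 + 2r). Assumed single-acquisition ICCs of 0.5, 0.7 and 0.9 become 0.75, 0.87 and 0.96. This reduces random error only. A fixed directional shift remains, and it grows in SD units as the residual SD shrinks.

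**5. What the triplicates could provide**

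The within-woman, within-session SD has n × (3 − 1) degrees of freedom. Its 95% limits, as multiples of the estimate, are √(df/χ²(0.975)) and √(df/χ²(0.025)):

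- one visit: df = 50 × 2 = 100, limits 0.88 to 1.16;
- three visits pooled: df = 300, limits 0.93 to 1.09.

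That is adequate precision for each muscle and condition without further scans.

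**The case against.** **Silence is not unblinding.** A reader might infer that the reader is unblinded, or that masking was considered and rejected. The article supports neither; it says nothing on the matter. A condensed article may also leave reading order and repeatability to a full protocol or SAP. This stands as to wording. The point still has substance, because the article describes acquisition, outlining and replicate handling in detail, raises reproducibility itself, and settles it by expectation.

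**Clips can be reread.** A reader might infer that a reading shift could never be separated from a real rise. That is too strong: recorded clips, if kept, can be coded and outlined again. Building this in beforehand is simply better than a repair.

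**Group tests already carry random error.** A reader might infer that without an error estimate no result can be interpreted. That is not so. Random error is in the spread of the within-woman changes and so already affects the Friedman test. A smallest detectable change concerns an individual, whereas the primary criterion concerns the cohort.

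**Triplicates answer only part of the question.** Taken in one session by one operator, they show neither between-visit error nor expectation bias, and in contraction they also contain variation in effort. This stands and limits how they may be used.

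**There are safeguards.** A single operator removes between-operator variance, measurement sites are anatomically defined, and rest and stretch values are averaged over the clip and over three acquisitions. The peripheral muscles would partly reveal general technical drift, though less so a muscle-specific expectation, since a different biceps pattern is expected. The study is also declared descriptive and exploratory. These points lower the stakes; none addresses a directional shift in outlining.

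**Conclusion.** The concern holds as a cheap and worthwhile improvement, not as an error or contradiction. A subjective reading step determines the primary outcome, the expected direction is stated, there is no control group, and no masking of clips to visit is described. A directional reading shift would therefore be confounded with gestation. Separately, the acknowledged lack of reproducibility data is met by expectation although replicates are already being collected.

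The size of any shift is unknown. The rejection rates above depend on assumed drifts and independent normal residuals. A reader might take the paired-test result to mean that about half of such studies would be falsely positive. It does not: the figure follows from setting the shift equal to the critical half-width, and under the planned Friedman test the same shift gives about 32% to 40%. The conclusion also rests on reading the single investigator as the person who outlines the regions.

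**What to change.** 1. Code the exported clips so that they carry no name, date or visit.
2. Have the same investigator outline the regions in random visit order, after a woman's three visits are complete and before her delivery data are opened. The latter also protects the secondary analysis of last-visit shear modulus against mode of delivery and tears.
3. State that masking covers the reading step only. Probe placement and the coaching of Valsalva and contraction remain open to knowledge of gestation.
4. Keep the mean of three for the main analysis. In addition, report the within-session ICC and standard error of measurement from the existing triplicates, per muscle and condition. Label them as within-session error, a lower bound on between-visit error, and do not use them as a threshold for visit changes.

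Cost: file coding, a random reading list and a small additional analysis. No second reader, extra scan or extra visit is needed. The drawback is that reading waits until each woman's visits are complete. If the full protocol or SAP already provides for this, one sentence in the article is enough.
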